**STUDY PROTOCOL**

# [name]*, [name], [name]

**Abstract**

**Background:** Animal studies have confirmed that statins have neuroprotective effects during and following a subarachnoid hemor- rhage; however, the therapeutic effect of statins in humans remains controversial. The interpretation of data currently available on the clinical application of statins to spontaneous subarachnoid hemorrhage is limited by the small sample sizes used in the studies, making it difficult to draw valid conclusions regarding the multiple neuroprotective effects of statins. Thus, we propose to perform a random- ized double-blind placebo-controlled parallel-group clinical trial to determine the effects of atorvastatin on spontaneous subarachnoid hemorrhage, apoptosis-related factors, and serum inflammatory factors in cerebrospinal fluid and to observe its neuroprotective effect mediated by relieving vasospasm.

**Methods/Design:** This is a randomized parallel-group placebo-controlled double-blind clinical trial. This trial will recruit 300 patients with spontaneous subarachnoid hemorrhage from the Department of Neurosurgery, 101st Hospital of PLA (Wuxi Taihu Hospital), Renmin Hospital of Wuhan University. These patients will be equally and randomly assigned to atorvastatin (20 mg/day) and placebo control groups. Outcomes will be evaluated at baseline, 3, 5, and 14 days after hemorrhage, and 6 months after discharge. The primary endpoint assessed GOS at 6 months after aSAH, dichotomized as good (≥4) or poor (<4) outcome. The second primary efficacy endpoint assessed all-cause mortality at 30 days after aSAH, CVS, vasospasm-related new infarction and delayed ischaemic neurological deficit(DIND) due to vasospasm within 2 weeks post-aSAH.

**Discussion:** The results of this trial will provide data on the clinical application and neuroregenerative effect of atorvastatin in the acute stage of spontaneous subarachnoid hemorrhage.

**Trial registration:** This trial was registered with the Chinese Clinical Trial Registry (ChiCTR-IPR-14005395) on 18 May 2014.

**Key words:** clinical trial; atorvastatin; spontaneous subarachnoid hemorrhage; statins; randomized controlled trial

**Funding:** This study was supported by the Army Scientific Research Foundation of Nanjing Military Region of Chinese PLA; the Foundation of the 101 Hospital of Chinese PLA

**introduction**

Subarachnoid hemorrhage mainly refers to when a trau- matic or non-traumatic intracranial hemorrhage, caused by a variety of reasons, induces blood to flow into the subarachnoid space (Welty and Horner, 1990; King and Martin, 1994). Non-traumatic subarachnoid hemorrhage is also known as spontaneous subarachnoid hemorrhage. Blood gathered in the subarachnoid space can cause severe inflammation as well as an increase in nitric oxide, en- dothelin, oxyhemoglobin, and proinflammatory cytokine levels. The collected blood may also lead to vascular spasm, stenosis, and ischemic brain damage, resulting in early brain injury and cerebral vasospasm. Early brain injury and cerebral vasospasm are the main causes of neurological dysfunction and death after subarachnoid hemorrhage (Sobey and Faraci, 1998; Tseng et al., 2005; Rabinstein, 2011). The delayed neurological dysfunc- tion caused by spontaneous subarachnoid hemorrhage is not primarily caused by vascular spasm, but is possibly due to early vascular dysfunction, indicating that early administration of drugs for endothelial protection may be beneficial to the prognosis of patients. Cerda et al. (2015) verified that in addition to lowering lipid, statins improve endothelial function by reducing oxygen free radical production and increasing nitric oxide synthesis in endothelial cells. Statins resist platelet aggregation (Kato et al., 2004; Antoniades et al., 2011; Luzak et al., 2012) and antagonize coagulation factor VII activity (Ural and Avcu, 2006; Dietzen et al., 2007) by elevating nitric oxide synthase activity. Statins also improve overall fibrinolytic activity, reduce the inflammatory response, maintain the integrity of the blood-brain barrier, and ease cerebral vasospasm to mitigate subarachnoid hemorrhage (Cheng et al., 2009).

Many animal studies have shown that statins have neu- roprotective effects on subarachnoid hemorrhage (Tseng et al., 2005; Chou et al., 2008; McGirt et al., 2009; Ver- gouwen et al., 2009; Garg et al., 2013; Kirkpatrick et al., 2014; Yoshimura et al., 2014), but its clinical therapeutic effects remain controversial. Garg et al. (2013) confirmed that simvastatin may relieve cerebral vasospasm after sub- arachnoid hemorrhage, but cannot improve patient outcome. At present, there are few data concerning clinical applica- tion of statins in patients with spontaneous subarachnoid hemorrhage, and those studies that do exist have small sample sizes. To reach a convincing conclusion, the results of a large-sample, double-blind, randomized, placebo- controlled trial are needed. Thus, the present proposed ran- domized, parallel-group, placebo-controlled, double-blind clinical trial has been designed to determine the effects of atorvastatin on spontaneous subarachnoid hemorrhage,

apoptosis-related factors, and serum inflammatory factors in cerebrospinal fluid.

**Methods/design**

## Study design

This randomized, parallel-group, placebo-controlled, double-blind clinical trial will be conducted in the De- partment of Neurosurgery at 101st Hospital of PLA (Wuxi Taihu Hospital) and Renmin Hospital of Wuhan University.

## Ethical considerations and informed consent

An investigator or investigator-authorized personnel will explain the benefits and risks of participation to the study to each patient, family member, and guardian and obtain written informed consent. This project has obtained the written approval of the Medical Ethics Committee of 101st Hospital of PLA (Wuxi Taihu Hospital) (approval No. 2014-YXLL-001) and is in accordance with the guidelines of the *Declaration of Helsinki*, formulated by the World Medical Association.

## Study participants

Patients with spontaneous subarachnoid hemorrhage hospitalized in the Department of Neurosurgery at 101st Hospital of PLA and Renmin Hospital of Wuhan University will be recruited to participate in this study.

### *Inclusion criteria*

Patients meeting all of the following criteria will be con- sidered for admission to the trial:

- Aged 60–90 years; both sexes
- Sudden severe headache, vomiting, and meningeal ir-

ritation (Suarez, 2015)

- Abnormal computed tomography (CT) scans of the brain or a lumbar puncture showing that the cerebro- spinal fluid is bloody and under increased pressure (Smith et al., 2013; Suarez, 2015)
- First onset of symptoms
- Time of atorvastatin administration is within 72 hours after hemorrhage
- Informed consent of patients or their family members

### *Exclusion criteria*

Patients presenting with one of the following criteria will be excluded from the trial:

- Traumatic subarachnoid hemorrhage
- Hyperlipidemia combined with diabetes mellitus
- Abnormal liver enzymes, myopathy, and rhabdomyolysis
- History of mental illness or epilepsy
- Serious heart and lung disease or multiple organ dys- function
- Recent chemotherapy and radiotherapy
- Currently participating in other clinical trials

## Randomization

The 300 participants will be numbered according to their time of admission by a statistician using a table of random numbers. The participants will be equally assigned to either the atorvastatin group or a placebo control group. Doctors, patients, and assessors will be blinded regarding patient group assignments to avoid measurement bias.

## Blinding and emergency unblinding

The treatment program for each participant will be gener- ated using a random allocation sequence and placed in ordered, sealed, opaque envelopes. The blinded codes will be preserved by the drug administrator. If a patient has a serious adverse event and it is necessary to immediately determine the drug administered, a principal investigator of the research unit will open that patient’s envelope. Once

the data are unmasked, the patient will be discontinued from the trial. The clinical research associate will be informed of the result. Researchers will record the reason and date of the unmasking and sign the case report form.

## Interventions

Patients in both groups will receive conventional treat- ments, such as sedation, absolute bed rest, fluid balance, and hemostasis.

Atorvastatin group: in addition to the conventional treat- ments, patients will be orally administered atorvastatin (trade name: Lipitor; approval No. GYZZ H2005140; Pfizer Dalian Pharmaceutical Plant, Dalian, China), 20 mg for each day.

Placebo control group: in addition to the conventional treatments, patients will be orally administered placebo (starch tablets with the same appearance as atorvastatin). The dosage will be consistent with that for atorvastatin.

A flow chart for this clinical trial is shown in **Figure 1** and **Figure 2**.

[figure not shown]

Figure 1

[figure not shown]

Figure 2

## Outcome measures

### *Primary outcomes*

- The primary endpoint assessed GOS at 6 months after aSAH, dichotomized as good (≥4) or poor (<4) outcome.

### *Secondary outcomes*

The second primary efficacy endpoint assessed all-cause mortality at 30 days after aSAH, CVS, vasospasm-related new infarction and delayed ischaemic neurological deficit(DIND) due to vasospasm within 2 weeks post-aSAH.

The defined of CVS, vasospasm-related new infarction and DIND can be consult at previously study as follows:

Angiographic vasospasm was defined as focal or generalized reduction of cerebral arterial caliber on conventional cerebral angiogram. TCD vasospasm was defined as any peak systolic middle cerebral artery velocity (PSVMCA) ＞200 cm/s and a Lindegaard ratio of ＞3. Vasospasm-related new infarction was defined that vasospasm was the relevant contributing factor or primary cause, and the development of a new lesion consistent with infarction on CT or MRI. DIND was defined as any 2 or more point fall in Glasgow Coma Scale or unaccountable new focal neurological deficit lasting ≥2 hours.

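### The DIND definition does not carry the vasospasm attribution of its own endpoint line, and nothing excludes events before randomisation, most clearly for CVS

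*Protocol*

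**What the plan says.** The protocol's Secondary outcomes section lists "delayed ischaemic neurological deficit(DIND) due to vasospasm within 2 weeks post-aSAH", together with 30-day mortality, CVS and vasospasm-related new infarction. It then defines the components. For DIND it says: "DIND was defined as any 2 or more point fall in Glasgow Coma Scale or unaccountable new focal neurological deficit lasting ≥2 hours".

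The neighbouring definitions are built differently. New infarction must have vasospasm as a contributing or main cause and must show as a new lesion on imaging. Vasospasm itself is defined by arterial narrowing on angiography, or by a transcranial Doppler velocity and ratio threshold. Neither vasospasm definition requires the finding to be new.

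Three other places matter:

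- Interventions: conventional care in both groups is described as "such as sedation, absolute bed rest, fluid balance" and haemostasis.
- Inclusion criteria: "Time of atorvastatin administration is within 72 hours after hemorrhage".
- Abstract: "Outcomes will be evaluated at baseline, 3, 5, and 14 days after hemorrhage, and 6 months after discharge".

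**The concern.** The endpoint line and the definition disagree on cause. The line asks for a deficit produced by vasospasm. The definition admits any fall of at least two GCS points. On its most natural reading, the condition that the deficit be unexplained belongs to the focal-deficit limb only. Sedation can lower the GCS and is named as background care, so a patient could meet the GCS limb without ischaemia. Two blinded assessors following the same text could classify that patient differently.

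The timing raises a second problem. The two weeks run from haemorrhage, but study drug may start as late as 72 hours afterwards. An event in that interval cannot be affected by the drug, and no sentence removes it from the count.

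Relief of vasospasm is a stated aim of the trial, so these components carry its mechanistic argument. Misclassified events would blur that argument.

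**Working it through.** **Step 1. Compare the definitions on cause and novelty.**

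| Component | Cause required in the definition? | New finding required? |
|---|---|---|
| New infarction | Yes, vasospasm | Yes |
| DIND, focal limb | Only that it is unexplained | Yes |
| DIND, GCS limb | Not clearly; the endpoint line alone supplies it | A fall implies change, but from no named value |
| CVS (angiographic or Doppler) | Not applicable | No |

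The protocol writes causation into the infarction definition and does not repeat it for DIND. CVS is the component with no novelty condition at all.

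**Step 2. Time before treatment.** The window is 14 × 24 = 336 hours. The latest permitted first dose is at 72 hours, so at most 72/336 = 21% of the window can precede any drug. The day-3 assessment is also at 72 hours from haemorrhage, so for a late starter it may precede or coincide with the first dose. The protocol does not state the interval between randomisation and first dose.

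**Step 3. Effect of extra events on the comparison.** The protocol states no DIND rate, no expected effect on DIND and no power for it; its sample size concerns the Glasgow Outcome Scale. There is therefore no figure of the plan's to reproduce here, and what follows is illustration.

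Inputs:

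- From the protocol: 300 patients allocated equally ("The participants will be equally assigned to either the atorvastatin group or a placebo control group"), so n = 150 per arm; two-sided 5% level.
- Assumed: the true DIND rates p, and a share q of the remaining patients, equal in both arms, who meet the definition through an event the drug cannot affect.

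Formulas:

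- Observed rate = q + (1 − q)p, so the observed difference is (1 − q) times the true difference.
- Power = Φ(z), with z = [d√n − 1.96√(2p̄(1 − p̄))] / √(p₁(1 − p₁) + p₂(1 − p₂)), where p₁ and p₂ are the observed rates, d is their difference and p̄ their mean.

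Worked case, true rates 30% versus 18%:

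- q = 0: d = 0.12 and p̄ = 0.24, so z = (1.470 − 1.184)/0.598 = 0.478 and power is 68%.
- q = 0.20: the rates become 0.20 + 0.80 × 0.30 = 0.440 and 0.20 + 0.80 × 0.18 = 0.344, so d = 0.096 and p̄ = 0.392. Then z = (1.176 − 1.353)/0.687 = −0.258 and power is 40%.
- For q = 0, 5%, 10% and 20%, the difference is 12.0, 11.4, 10.8 and 9.6 points, and the risk ratio is 0.60, 0.66, 0.71 and 0.78.

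Power over a range of assumed rates:

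| True rates (placebo vs atorvastatin) | q = 0 | 5% | 10% | 20% |
|---|---|---|---|---|
| 30% vs 18% | 68% | 60% | 52% | 40% |
| 30% vs 15% | 88% | 80% | 72% | 57% |
| 20% vs 10% | 68% | 55% | 45% | 32% |
| 40% vs 24% | 85% | 79% | 73% | 61% |

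The direction is the same in every row. The size depends wholly on the assumed p and q.

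**The case against.** The strongest reply is that the endpoint line and the definition should be read together: an event must meet the definition and also be due to vasospasm. On that reading, a fall caused by sedation is already excluded. A reader might infer from the word *any* that every two-point fall counts whatever its cause. The document does not support that, because the endpoint line carries the attribution. It is also arguable grammatically whether the conditions of being unexplained and lasting two hours cover the GCS limb. What remains is that the attribution is missing from the sentence an assessor would apply, and no rule is given for applying it.

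A second reply concerns sedation. The definition needs a fall, and sedation already present at the reference assessment produces none. Sedation is only listed as an example of care, with no depth or timing. This stands: how often sedation would create a qualifying fall is unknown. It also shows why an unnamed reference GCS matters.

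Third, a reader might infer that all deterioration before randomisation is counted. That goes too far for DIND and infarction, where a fall or a new deficit or lesion implies change and a baseline evaluation exists. The gap is plainest for CVS. In addition, 72 hours is a limit and not a typical delay.

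Finally, adjudication detail may sit in an analysis plan that is not at hand. That is fair for procedure, but the protocol itself fixes this definition, and the mismatch lies within it.

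**Conclusion.** The point holds as an internal inconsistency to be reconciled. The endpoint names a cause that its definition does not clearly require for the GCS limb, no reference GCS is given, and nothing excludes events before randomisation, most clearly for CVS.

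Dilution is a reasoned consequence, conditional on the extra events being about equally frequent in the two arms. It is not an amount the document supports. Under the assumed 5% to 20% of extra events, power drops by about 8 to 28 points for 30% versus 18% (68% to between 60% and 40%) and by about 8 to 31 points for 30% versus 15% (88% to between 80% and 57%). With few such events the loss is small: at 5%, a 12.0-point difference becomes 11.4.

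This affects components of the secondary endpoint. The primary outcome at six months is untouched. The change should be made, but the trial does not stand or fall on it.

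**What to change.** Reconcile the DIND definition with its endpoint line. Both limbs should require:

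- a change from a named reference GCS or neurological state;
- a duration of at least two hours;
- no other explanation, sedation included, in the judgement of the existing blinded assessor.

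Count CVS, infarction and DIND only if new since randomisation, up to the two-week limit already stated. The 72-hour eligibility criterion needs no rewording for this purpose.

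The cost is a change of wording and one item for cause on the case report form; assessors are already blinded. Some judgement enters the classification. Late starters get a somewhat shorter period at risk, which randomisation balances across the arms.

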## Follow-up

The participants will be followed up 6 months after discharge. The patients will be requested by telephone to return to the hospital for examinations that will include CT angiography plus CT perfusion imaging, conventional CT, blood testing, cerebrospinal fluid analysis, transcranial Doppler ultrasonography, and neurological scale assessments. If a patient is lost to follow-up, the last values assessed will be considered the values for the 6-month follow-up.

## Safety

Adverse reactions may include gastrointestinal dysfunction, immune system dysfunction, insomnia, forgetfulness, nervous system dysfunction, pruritus, myalgia, arthralgia, and serum transaminase and phosphocreatine kinase abnormalities.

To facilitate truthful reporting by patients of the changes in their conditions after drug use, the doctors will avoid asking patients leading questions. Adverse events or un- anticipated side effects (symptoms, signs, and laboratory tests) will be recorded in addition to the curative effects.

If severe adverse events occur, researchers will immediately take appropriate therapeutic measures. The drug will be withdrawn. Drug withdrawal time, adverse events, symptoms, occurrence time, duration, treatment, and out- come will be recorded. The investigators will report all severe adverse events to the responsible unit, reporting units, the ethics committee, the Drug Supervision and Ad- ministration Department, and the relevant administrative departments within 24 hours. The investigators will sign and date the report.

## Data management

The medical records will be electronically saved on a computer. The accuracy of data recorded on the case data form will be verified. Any changes or corrections will retain a clear record of the original. The investigator will record the date of changes or corrections, sign his or her name, and explain the reasons for the change (if necessary). The medical records along with any changes, deletions, or additions will be electronically saved on a computer. The audit trail will be set so that it is protected by the system and will not be able to be modified or edited by anyone. The clinical data management system will have authority management such that only authorized personnel will be allowed to operate it. The use of an electronic signature is a common means of managing electronic management systems. Only authorized personnel can log onto the system for data entry or modification or to view the data, preventing unauthorized logins and access to any clinical data so that it remains secure and confidential. In accordance with the China Drug Clinical Trial Management Specification, all records will be preserved for at least 5 years after completion of the trial.

## Trial quality assurance and control

[name], one of the authors, will be responsible for quality assurance and control. A clinical research associate as- signed by the sponsor will visit the hospital regularly to ensure that the protocol has been strictly followed and that all data are correctly recorded. The researchers will implement standard operating procedures for clinical trials before, during, and after the trial. During the trial, inspectors will monitor the correctness and integrity of the data using case registration forms. Researchers will be provided with training to enable uniform recording methods and judgment standards. Researchers will carefully record all information on case report forms to ensure that the data are correct and reliable. The investigators will use normal reference ranges as standards to determine abnormal laboratory test results. All observations and findings will be checked to ensure data reliability and to ensure that the conclusions come from the original data. In the clinical trials and data processing stage, there will be corresponding data management measures. Active measures will be taken to control the dropout rate to within 20%.

**discussion**

Sedation, absolute bed rest, fluid balance, and hemostasis are for the symptomatic treatment of patients with spontaneous subarachnoid hemorrhage. Such conventional treatments cannot effectively restore the patient’s neurological

condition. Thus, the goal of this study is to confirm the multiple neuroprotective effects of atorvastatin, including reducing inflammation, relieving vasospasm, improving endothelial cell function, and confronting blood coagula- tion activity in the treatment of spontaneous subarachnoid hemorrhage through this clinical trial. It remains poorly understood whether the addition of atorvastatin to the treatment protocol will improve outcome in the recovery of neurological function. The most common adverse reaction of atorvastatin is myopathy, which resolves after drug withdrawal because it occurs with atorvastatin administra- tion in a dose-dependent manner (Hermann et al., 2006; Soininen et al., 2006; Abdelbaset et al., 2014). The effect of atorvastatin on liver function is limited (Gershovich and Lyman, 2004; Tikkanen et al., 2013; Kalantari and Naghipour, 2014). Therefore, atorvastatin is expected to become a relatively safe method for the treatment of spontaneous subarachnoid hemorrhage. If this large sample size, ran- domized, parallel-group, placebo-controlled, double-blind clinical trial verifies the effectiveness of atorvastatin, this drug will be considered effective for the treatment of spontaneous subarachnoid hemorrhage.

## Trial status

Ongoing and recruiting at the time of submission.

